## Abstract

**Introduction:**

Parkinson's disease (PD) with mild cognitive impairment (MCI-PD) or dementia (PDD) and dementia with Lewy bodies (DLB) are characterised by motor and ‘non-motor’ symptoms which impact on quality of life. Treatment options are generally limited to pharmacological approaches. We developed a psychosocial intervention to improve cognition, quality of life and companion burden for people with MCI-PD, PDD or DLB. Here, we describe the protocol for a single-blind randomised controlled trial to assess feasibility, acceptability and tolerability of the intervention and to evaluate treatment implementation. The interaction among the intervention and selected outcome measures and the efficacy of this intervention in improving cognition for people with MCI-PD, PDD or DLB will also be explored.

**Methods and analysis:**

Dyads will be randomised into two treatment arms to receive either ‘treatment as usual’ (TAU) or cognitive stimulation therapy specifically adapted for Parkinson's-related dementias (CST-PD), involving 30 min sessions delivered at home by the study companion three times per week over 10 weeks. A mixed-methods approach will be used to collect data on the operational aspects of the trial and treatment implementation. This will involve diary keeping, telephone follow-ups, dyad checklists and researcher ratings. Analysis will include descriptive statistics summarising recruitment, acceptability and tolerance of the intervention, and treatment implementation. To pilot an outcome measure of efficacy, we will undertake an inferential analysis to test our hypothesis that compared with TAU, CST-PD improves cognition. Qualitative approaches using thematic analysis will also be applied. Our findings will inform a larger definitive trial.

**Ethics and dissemination:**

Ethical opinion was granted (REC reference: 15/YH/0531). Findings will be published in peer-reviewed journals and at conferences. We will prepare reports for dissemination by organisations involved with PD and dementia.

**Trial registration number:**

ISRCTN (ISRCTN11455062).

Strengths and limitations of this studyThe use of psychosocial therapies for cognitive impairment in movement disorders is important and under-researched.This study uses a range of process and exploratory measures to ascertain the feasibility of undertaking a large efficacy randomised controlled trial powered to assess a range of complex outcomes in both affected participants and their companions.The efficacy of the intervention in improving cognition will be evaluated.Dyads will be recruited from multiple clinical sites to reduce potential bias when recruiting from a single site.Recruiting to target will be a challenge, due to the complexity of the intervention, the relative frailty of some participants and the existing responsibilities of the companion.

## Introduction

### Background and rationale

Within the spectrum of Lewy body disorders, cognitive impairment can manifest as Parkinson's disease (PD) dementia (PDD), Parkinson's disease with mild cognitive impairment (MCI-PD) and dementia with Lewy bodies (DLB). Only very limited drug-based treatments are available for PDD, and no medications have been licensed for MCI-PD and DLB. Without adequate management of the non-motor aspects of these conditions, the risk of being admitted to care is very high. Increasing the availability and the evidence base for non-drug-based therapies for dementia and mild cognitive impairment, such as psychosocial interventions, is a key objective of England's National Dementia Strategy^1^ and other national dementia policy drivers. Unfortunately, there is almost no evidence to support their use in people with more complex forms of dementia, such as dementias associated with Parkinson's-related disorders.^2^ Thus, there is a need to extend psychosocial therapies to this population. Unpublished data provided by public and patient involvement (PPI) representatives and Parkinson's expert consultees involved in this project support this view.

For people with dementia unrelated to Parkinson's-related disorders, psychosocial therapies, such as reality orientation or reminiscence therapy, have been in use for some time.^3^ Recently, in the UK, several large-scale multicentred trials of psychosocial interventions for dementia have been conducted, for example, goal-oriented cognitive rehabilitation^4^ and individual cognitive stimulation therapy (iCST)^5^; however, these have either specifically excluded people with PD/DLB or not been tailored to meet their needs. One of the most widely accepted psychosocial therapies for dementia, which has been accepted for use in the National Health Service (NHS) and is part of the National Institute for Health and Care Excellence^6^ guidelines for dementia care is structured group cognitive stimulation therapy (CST).^7^ Based on these recommendations, as well as its relatively widespread use and availability, CST was chosen by the research team as a candidate therapy to adapt for individuals with Parkinson's-related dementias.

CST was originally developed from a Cochrane systematic review of psychological interventions for people with dementia^8^ and has been shown to be cost-effective, to improve quality of life and to enhance cognition to an extent comparable with trials of cholinesterase inhibitors.^5–7^ CST is based on the principle that stimulating engagement in cognitive and social activity enhances cognitive function and quality of life. However, in spite of the success of the therapy in a group setting, it was recognised that not all people with dementia may have access to, or wish to participate in, group activities. CST was therefore adapted for home-based individualised administration (via a study companion) in the form of ‘individual CST’ (iCST).^5^

The efficacy of iCST was recently investigated in a 26-week multicentre, single-blind, randomised controlled trial (RCT).^5^ The findings revealed a significant improvement in the quality of the relationship of the person with dementia and their study companion, as well as an improvement in health-related quality of life for companions (designated ‘caregivers’). Furthermore, iCST was found to be feasible for people who found travel a barrier to participation. Outcomes related to those who support or care are particularly important, since the perceived burden of care has been shown to be significantly related to the extent of associated cognitive impairment in the person living with Parkinson's-related dementia.^9^ This may be in part due to the added responsibility of managing the impact of concurrent cognitive, psychiatric and physical impairments in the cognitively impaired person. Nonetheless, in spite of the positive findings mentioned above, iCST did not appear to improve cognition or quality of life of the cognitively impaired participants themselves.

While CST as a psychosocial intervention for people with Parkinson's-related dementia has potential, early consultation with PPI and Parkinson's expert groups suggested the need for adaptation. Thus, the first step was to undertake a ‘therapy adaptation’ process in order to meet the specific needs of people with PDD, MCI-PD or DLB. This will be described in detail in a subsequent paper. The adaptation was deemed necessary due to the added complexity of the symptoms related to PD which may include frequent episodes of confusion, marked hallucinations and delusions, high rates of apathy, a myriad of motor symptoms and dependency on companions due to physical disability. It was hypothesised that cognitive stimulation therapy specifically adapted for Parkinson's-related dementias (CST-PD) may improve cognitive function and quality of life in this population and could potentially have a positive effect on companions and other outcomes.

The protocol outlined here describes a feasibility and exploratory study embedded within a pilot trial of CST-PD, which will be delivered by companions. This study will address some of the iterative steps in the process involved in developing a complex intervention for people with dementia, as outlined by the UK's Medical Research Council (MRC) guidance on the topic.^10^ First, it is a test to explore whether it is possible to implement and evaluate this particular complex intervention, including aspects of treatment implementation and dosing, and second, it will be a small-scale trial of the intervention to estimate the treatment effect and its variance on a single main outcome as well as exploratory subsidiary outcomes.

### Overall aim

The purpose of this work is to gather the information needed to design a subsequent full-scale, definitive RCT powered to evaluate the efficacy of CST-PD in improving a range of outcomes relevant to people with PDD, MCI-PD or DLB and their companions.

### Objectives

To fulfil our aim, we will achieve the following objectives:

Primary objectivesAn evaluation of the operational aspects of the study including recruitment, acceptance of the intervention and assessments, and loss to follow-up;A process evaluation of the intervention including whether the intervention can be delivered, received and enacted as intended,^11^ as well as acceptability and tolerability of the intervention by the dyads (people with MCI-PD, PDD or DLB, referred to as participants, and their study partners, referred to as companions).

Secondary objectivesAn exploration of the potential efficacy of the intervention on a single primary outcome, cognition;An exploration of the potential possible outcome measures in terms of feasibility, clinically meaningful change and relationship to the intervention.

### Research questions and hypotheses

The following are research questions for the feasibility and exploratory study:Is it possible to recruit sufficient dyads in a timely manner?What is the acceptability and tolerability of the intervention by dyads?Which are the most clinically meaningful and acceptable outcomes by which to assess efficacy?Based on the findings, what would the sample size of a fully powered definitive RCT of the intervention be?

The following is the hypothesis to explore potential efficacy of the intervention:In people with PDD, MCI-PD or DLB, the change in cognitive function from baseline to withdrawal of CST-PD at 12 weeks will favour the intervention compared with treatment as usual (TAU).

## Methods

This protocol was prepared in accordance with SPIRIT 2013 statement^12^ (checklist is available as an online supplementary file). The trial is registered with the ISRCNT (ISRCTN11455062); all study-related items from the WHO Trial Registration Data Set are available at the registry. The protocol lies within a research programme comprising a series of sequential steps in the development, feasibility testing, piloting and eventual full-scale trialling of a complex psychosocial intervention for people with PDD, MCI-PD or DLB. The programme has followed the UK's MRC's updated Guidance on ‘Developing and Evaluating Complex Interventions^10^ and is now at the feasibility, exploratory and pilot trial stage, which we describe here. Specifically, this part of the programme is a fully controlled randomised single-blind exploratory pilot trial with an embedded feasibility process evaluation and evaluation of new outcomes. The protocol for the process evaluation is not reported here but will form the basis of other papers. The pilot trial is designed and powered to test the hypothesis that CST-PD is superior to TAU for people with PDD, MCI-PD or DLB in improving cognitive function when assessed at baseline and 12 weeks post-randomisation. The therapy will be delivered in participants’ homes with recruiting sites in locations in Greater Manchester and other regions in the UK. A CONSORT-style flow chart for the trial is shown in figure 1.

10.1136/bmjopen-2017-016801.supp1Supplementary material 1

**Figure 1 F1:**
[figure not shown]
CONSORT-style flow chart.

The feasibility study is designed to (1) ascertain the feasibility of conducting the trial in a small scale and (2) explore secondary outcomes for which the trial is not powered to detect efficacy. It is vital to address these issues, since in the case of an intervention such as CST-PD, there are multiple components working in synergy to produce change, and it is not clear at the outset which components may result in change and at which level this may occur (eg, individual, companion, relationship and so on).^10^ Thus, the ‘dimensions of complexity’ highlighted in the MRC's new guidance for developing and evaluating complex interventions^10^ that need to be considered and accounted for in the trial design are outlined in table 1. A single team will evaluate the three sets of outcomes (efficacy trial, feasibility study and exploratory study) in order to foster an ongoing process of integration of evidence as to the conduct of the different steps in the study and trial, as suggested by Moore *et al*.^13^

**Table 1 T1:** Description of ‘dimensions of complexity’ in the adapted study as per MRC's guidelines^10^

Dimension	Reason for complexity
Number of and interactions between components within the experimental interventions	Since the intervention will be delivered by the companion and we anticipate that no two companions or participants will have the same skills, interests or deficits, there may be a degree of variation in each therapy session. The therapy is based on this assumption and is designed to maximise outcomes by adopting a person-centred approach. Participants choose the activities they are most interested in from a library of over 60 cognitively stimulating topics. Companions subsequently personalise the activity through verbal, visual, tactile, auditory, gustatory or olfactory cues. Thus, the therapy subscribes to a structured, yet tailored, approach, delivering an intervention that is standardised with respect to dose and delivery but variable with respect to content.
Number and difficulty of behaviours required by those delivering or receiving the intervention	Standardised companion training is critical to minimise heterogeneity. All companions will be trained to criterion and their skills monitored over time. This element of treatment fidelity will reduce the likelihood of non-significant results at the end of the study being attributed to poor training rather than an ineffective intervention. Companions will receive a minimum of 2 hours training and must have sufficient cognitive function (by not meeting clinical criteria for dementia) to be able to deliver the therapy. Companions’ ability to deliver the therapy will be self-assessed and researcher rated at the end of the training and monitored throughout the study.
Number and variability of outcomes	Although the trial is powered to assess cognitive functioning as the main outcome, it is likely that there may be effects on different outcomes such as behaviour, companion variables, relationship features and health economic issues.
A good theoretical understanding is needed of how the intervention causes change, so that weak links in the causal chain can be identified and strengthened	The background literature of evidence of potential mechanisms, as well as clinical experience, has suggested that each function of the intervention can be linked to identifiable intermediate impacts and final outcomes and can be outlined in a logic model^32 33^ which will be outlined elsewhere.

MRC, Medical Research Council.

### Dyad selection

Sixty-four dyads will be asked to participate. Inclusion and exclusion criteria are listed in table 2.

**Table 2 T2:** Inclusion and exclusion criteria for participants and companions

**Inclusion criteria—participant**	**Exclusion criteria—participant**
Have a diagnosis of possible or probable PDD, MCI-PD or DLB. Diagnosis will be based on standard clinical diagnostic criteria^34–36^ determined by the referring clinician and verified on screening.	Lack sufficient physical and mental capability to participate in the therapy. Capability will be based on clinical impression at the initial screening visit and informed by scores obtained on the Schwab and England Activities of Daily Living Scale^22^ and MoCA.^21^
Be willing to participate in 30 min sessions of the intervention, three times per week.	Current involvement in any other dementia intervention research study.
Be on a stable on medication regimen for at least 4 weeks, prior to study entry.	Unable to understand conversational English, are non-literate or have physical or mental illness severe enough to preclude participation in the study.
	Living in residential care.
**Inclusion criteria—companion**	**Exclusion criteria—companion**
Provide care or support for a person with Parkinson's-related dementia.	Lack capacity to consent to the study to ensure and able to undertake the training and delivery of the intervention.
Be willing and well enough to deliver 30 min sessions of the intervention, three times per week.	Unable to understand conversational English, are non-literate or have physical or mental illness severe enough to preclude participation in the study.
Be familiar with the participant's physical and mental health and able to provide feedback about this to the study team.	A diagnosis of dementia; the presence of dementia in the companion will be determined by self-report as well as clinical impression informed by performance on the MoCA.^21^

DLB, dementia with Lewy bodies; MoCA, Montreal Cognitive Assessment; MCI-PD, Parkinson's disease with mild cognitive impairment; PDD, Parkinson's disease dementia.

We will recruit from centres based at Manchester, Warrington, North East London, and Derby, in the UK. Centres will have established memory or movement disorder clinics and high volumes of people with PDD, MCI-PD or DLB. As recruitment may be influenced by clinic closures during certain times of the year (eg, Christmas and the summer months), recruitment will be carried out over 15 months to obtain an accurate estimate of recruitment rate. The study will be advertised on UK-based charity websites (eg, Parkinson's UK, the Lewy Body Society) and through Join Dementia Research (https://www.joindementiaresearch.nihr.ac.uk). User-friendly information brochures (available as on online supplementary file) will be available at memory and movement disorder clinics and support groups, and information talks will be given at Parkinson's UK community groups. In a recent trial of iCST involving people with non-PD dementias and their companions, the recruitment target (356 dyads over 15 months) was achieved^5^; however, the level of companion burden experienced in the non-PD dementia population may be less compared with that experienced by companions of people with PDD, MCI-PD and DLB, and this may influence recruitment.^14^ Furthermore, Parkinson's-related dementia is much less common compared with dementia of the Alzheimer type.^15^ Therefore, one of the goals of this study is to obtain an accurate estimate of the recruitment rate for participants and their companions.

### Sample size

A predetermined sample size for the feasibility aspects of this study is not required, since inferential statistics will only be exploratory. The sample size is determined by that required to detect a clinical meaningful difference in our primary outcome measure, cognitive function. To determine sample size, we referred to the previous literature^7 8 16^ and, taking a conservative approach, have estimated the standardised effect size on cognition of the parent form of the intervention to be 0.4. Thus, assuming 80% power and a correlation coefficient of 0.5 between baseline and endpoint on cognitive outcomes, the required sample size is 27 completers per group. By enrolling 32 dyads per group, it will allow for a 15% attrition rate (consistent with pilot sample guidance^17^). For the secondary, exploratory outcomes, the proposed sample size of 27 per group is within the recommended guidelines (24–50 participants^18 19^) required to estimate the standard deviation (SD) for a sample size calculation.

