### ‘Treatment as usual’ (control) group

For the purposes of the feasibility evaluation, the inclusion of a control group (ie, TAU) is important because it allows for a more realistic evaluation of the operational aspects (ie, recruitment, retention and randomisation) as well as the implementation of the intervention.^23^ If conducted in an unblinded, non-randomised manner, the outcomes, particularly for a complex psychosocial intervention such as is being tested here, may be quite different. Furthermore, since previous evidence enabled us to power the primary outcome measure, cognitive function, for an evaluation of efficacy, a pilot trial was considered possible and this required inclusion of a control group to account for the natural progression of symptoms during the trial. Specifically, in the TAU comparator arm, dyads will not receive any additional intervention to their standard NHS treatment for PD and cognitive impairment or DLB. Typically, this involves dopamine replacement therapy for the symptomatic relief of Parkinsonism, cognitive enhancing medication (eg, cholinesterase inhibitors) and support from a Parkinson's disease nurse specialist. Since people with Parkinson's-related dementia tend to have significant symptoms in multiple domains, the support of occupational therapist, speech and language therapists and physiotherapists is often required. These interventions will be available to both the TAU as well as those dyads randomised to the active treatment arm. Treatment fidelity will be actively monitored in the control group, as it is in the experimental group, to ensure that the control group do not receive an active intervention component which could reduce the effect size between the experimental and control groups or, similarly, to ensure that an iatrogenic component is not added to the control group which could artificially inflate the difference in outcomes between the two groups.^24^

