#### Primary and exploratory outcome measures

The piloted efficacy and exploratory outcome measures for the participant are outlined in table 5a and the exploratory outcome measures for the companion in table 5b. The pilot efficacy measure on which the study has been powered is cognitive function as assessed using the Addenbrooke's Cognitive Examination III^26^ and the Everyday Cognition Questionnaire.^27^ Although the pilot trial has been powered on a previously reported effect size, the adaptation of the therapy and single outcome measure means that any potential treatment effects will be interpreted cautiously in order to not mislead the subsequent sample size and power calculation of the full RCT with multiple outcomes.^28^ With this caveat, we will test the hypothesis that compared with the TAU group, the difference in the total cognitive score between baseline and endpoint will be significantly greater in the experimental group. We will undertake a complete case analysis, only including trial completers without missing data, as well as an additional analysis based on last observation carried forward for dyads with missing data. Group differences in the change of outcome measures will be assessed using t-test or analysis of covariance adjusting for baseline differences, including cognitive stage at baseline.

**Table 5 T5:** Primary and exploratory outcome measures

Measure/author	Purpose	Time point

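### The effect size of 0.4 is labelled clinically meaningful and conservative without justification for companion-delivered CST-PD, and 27 completers per group do not give the efficacy power that the protocol claims

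*Protocol article*

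**What the plan says.** The Sample size section opens with the purpose of the calculation: "The sample size is determined by that required to detect a clinical meaningful difference in our primary outcome measure, cognitive function". The next sentence gives the effect size and its source: the authors, "taking a conservative approach, have estimated the standardised effect size on cognition of the parent form of the intervention to be 0.4", citing references 7, 8 and 16. The calculation then proceeds "assuming 80% power and a correlation coefficient of 0.5 between baseline and endpoint on cognitive outcomes", and concludes that "the required sample size is 27 completers per group". The significance level and sidedness are not stated.

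Three other places bear on this.

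- **Background and rationale.** CST is reported to enhance cognition. Of the home-based, companion-delivered form (reference 5), the section says that "iCST did not appear to improve cognition or quality of life of the cognitively impaired participants themselves".
- **Active intervention.** CST-PD is based on both conventional CST (reference 7) and iCST (reference 5). The Abstract confirms home delivery by the study companion.
- **Primary and exploratory outcome measures.** The exploratory variables are included partly to help establish what a clinically meaningful difference would be.

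The claim of adequate power also appears outside the Sample size section. The opening of the Methods describes the pilot as designed and powered to test superiority on cognition. The control-group section says a pilot trial was considered possible "since previous evidence enabled us to power the primary outcome measure, cognitive function, for an evaluation of efficacy".

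**The concern.** The section uses 0.4 in two roles. A clinically meaningful difference is the smallest effect worth detecting. An estimate from earlier trials is the effect one expects. The protocol supplies only the second and presents it as the first.

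The word *conservative* raises a separate problem. CST-PD has two parent forms, and the one with the same mode of delivery is iCST. The protocol itself reports iCST as showing no apparent cognitive gain, yet reference 5 is not among the sources for 0.4 and the section does not discuss it. An estimate that leaves out the less favourable parent has not been shown to be cautious for this trial.

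What is at stake is how the cognition result is read. The Summary says the trial will show whether there is enough evidence of efficacy to justify a larger trial. A reader told that the comparison has 80% power for a cautious and clinically meaningful effect would take a non-significant result as evidence against a worthwhile benefit. The design cannot support that reading.

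**Working it through.** **Inputs from the protocol.** Standardised effect 0.4; power 80%; baseline-endpoint correlation r = 0.5; 27 completers and 32 enrolled per group; attrition 15% (Sample size). Analysis by t-test on change or by ANCOVA (Primary and exploratory outcome measures). **Assumed:** two-sided 5%, equal SD at both time points, outcome SD = 1.

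**Step 1: the protocol's own figures.** Attrition reproduces: 27 / 0.85 = 31.8, rounded up to 32. The 27 does not reproduce.

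- SD of change = √(2(1 − 0.5)) = 1.
- ANCOVA residual SD = √(1 − 0.5²) = 0.866.
- Normal approximation, n per group = 2 × SD² × (1.960 + 0.842)² / 0.4².
- Change score: 2 × 1 × 7.849 / 0.16 = 98.1, so 99 (100 with the t distribution).
- ANCOVA: 2 × 0.75 × 7.849 / 0.16 = 73.6, so 74 (75 with the t distribution).

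The hypothesis is directional (the difference "will be significantly greater in the experimental group"), so a one-sided 5% test was also tried. It needs 78 (change) or 59 (ANCOVA) per group. Among t-test and ANCOVA settings with a standardised difference of 0.4, only ANCOVA at a one-sided level of 0.20 gives 27. F-test calculations that read the effect as Cohen's f (0.2 in a repeated-measures interaction, or 0.4 in ANCOVA) give 26 per group, but they correspond to a between-group effect of about 0.8. None of these settings is stated.

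**Step 2: power at 27 per group.** Noncentral t with 52 degrees of freedom and noncentrality (effect / SD) × √(27/2). At 0.4 the noncentrality is 0.4 × 3.674 = 1.47 (change) or 1.70 (ANCOVA).

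| True effect (SD) | Power, change score | Power, ANCOVA |
|---|---|---|
| 0.4 | 30% | 38% |
| 0.3 | 19% | 24% |
| 0.2 | 11% | 13% |
| 0.1 | 6.5% | 7% |

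One-sided 5% at 0.4 gives 42% / 51%. The effect detectable with 80% power (two-sided) is 0.78 / 0.67 SD.

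**Step 3: precision at 27 per group.** The 95% confidence interval half-width is 2.007 × SD × √(2/27) = 2.007 × 0.272 = 0.55 SD (change), or × 0.866 = 0.47 SD (ANCOVA). An estimate near zero would leave 0.4 inside the interval.

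**Step 4: how much weight the iCST result carries.** The Dyad selection section says the iCST trial met its target of 356 dyads. Assuming 1:1 allocation (178 per group) and the settings above, its power at 0.4 would be about 96% / 99%. With an assumed 25% loss (about 133 per group) it would be 90% / 96%. The result cannot be set aside as that of a small trial. The protocol gives no effect estimate or interval for it, so no size can be read from it.

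**The case against.** The strongest defence is that nothing here is a contradiction, and that is right. The protocol attributes 0.4 to the parent form, and the Background does report cognitive benefit for CST. The iCST trial studied people with non-PD dementias over 26 weeks, whereas CST-PD was adapted for this population. An effect can also be both clinically meaningful and cautiously estimated. The iCST result weakens the transfer of 0.4 to CST-PD but does not refute the parent-form estimate. Whether 0.4 is cautious relative to references 7, 8 and 16 cannot be checked from the document.

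A reader might go further and infer that the protocol's evidence points to an effect well below 0.4. No iCST effect size is given, so that is not supported. A reader might also infer that 0.4 will become the target for the definitive trial. No section plans this: the research questions derive that sample size from this study's findings, and the outcome-measures section promises cautious interpretation and aims a later trial at the smallest clinically meaningful difference.

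It can also be said that the low power at 27 per group comes mainly from the sample-size arithmetic and not from the choice of 0.4. That is largely true. At the 100 (change) or 75 (ANCOVA) per group that 0.4 really needs, power would be about 56% at 0.3 and 29% at 0.2. The two points should be corrected together, but correcting the arithmetic alone would leave both labels in place. The promise of cautious interpretation concerns the results and does not amend the claim of power.

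**Conclusion.** The point holds as a gap in justification together with a stated property that the design lacks. The label of clinically meaningful rests on no minimal important difference, and the protocol elsewhere treats that quantity as unknown. The label of conservative is unsupported for home, companion-delivered therapy while the iCST cognition result goes unaddressed. The statements that the trial is powered for efficacy on cognition are wrong under the named analyses: power at 0.4 is 30% to 38% instead of 80%, and between 6.5% and 24% for effects of 0.1 to 0.3.

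These figures assume a two-sided 5% level, r = 0.5 and 27 completers per group. A one-sided 5% test raises power at 0.4 only to 42% / 51%. It would be too absolute to say that no null result could exclude 0.4: an ANCOVA estimate below about −0.07 (0.40 − 0.47) would do so. An estimate around zero would not.

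Feasibility and acceptability are the primary objectives and are unaffected.

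**What to change.** Make these changes together with the correction of the sample-size arithmetic.

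1. **Sample size section.** Describe 0.4 as an effect assumed from the parent-form literature. Remove the descriptions of it as conservative and as a clinically meaningful difference. Cite the iCST cognition result and say why a different result might be expected after adaptation, if the authors hold that view.
2. **Same section.** Replace the statement of 80% power with a short table of power and expected confidence interval half-width for true effects of 0.1 to 0.4 at 27 completers per group. State the significance level, sidedness and analysis used.
3. **Opening of the Methods and the control-group section.** Replace the claim that cognition is powered for efficacy with a statement that the comparison is exploratory and estimates the effect with its confidence interval. The control arm remains justified by the other reasons that section gives, namely realistic recruitment, retention and randomisation, and allowance for natural progression.

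The cost is a few sentences and one small table, with no extra dyads. The drawback is a less favourable stated justification for the efficacy comparison.
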